# Acronyms and Abbreviations

ANC Antenatal care

CHW Community Health Worker

DHO District Health Officer

FGD Focus Group Discussions

HA Health Assistant

LMNP Last Normal Menstrual Period

MDGs Millennium Development Goals

MOH Ministry of Health

MS Medical Superintendent

UDHS Uganda Demographic and Health Survey

UNO United Nations Organisation

VHT Village Health Teams

WHO World Health Organisation

# Operational definition of terms

*Primary healthcare facility* The first contact point for formal healthcare - In this case the first contact for which pregnant women access antenatal care i.e. health centres II, III, IV and ANC services at hospitals

*Prenatal service* -as prescribed by the WHO history taking, physical examinations, laboratory investigation, prescriptions, administration of folic acid and Ferrous tablet, assessment for referral, dialogue and discussions about pregnancy, dangers in pregnancy, hygiene, immunisations and birth preparedness

*Technical maternal and newborn services*-more clinical services for example history taking, physical examination like palpation, drawing of blood samples, estimating pelvic adequacy and assessing for referral

*Less technical maternal and newborn services*-services of a promotional nature health education, counselling, birth preparation which entails dialogue and discussions with the pregnant women and their attendants/caregivers

*Individual ANC educational interventions*- information given to a pregnant woman attending ANC based on the unique problems or demands or needs that she presents with during the current pregnancy as opposed to uniform information provided to all prenatal women

*Consistent ANC visits*-timely and completed four ANC visits

*Health worker with a promotional profile* a health worker with a formal employment in the district health system, whose primary training is health prevention and health promotion, does not routinely take part in clinical services like physical examinations, prescriptions of medicines or surgery – in this case we refer to the Health Assistant (HA)

*Homecare practices*-care provided to prenatal women and newborn babies at home based on knowledge and perception of the care givers (elements of care considered in this study are: nutritional care for pregnant women, care for the cord, warmth for newborn babies, and initiation of breastfeeding and neonatal immunisation status)

*Elderly caregivers*-these are usually women in the households, about 50 years or older. They provide neonatal care and advice to family members within the household sometimes extending to the immediate neighbours. As opposed to TBAs, they are not transactional. They provide expert opinion and demonstrate actual care to postnatal women within the household or immediate neighbourhood

*Institutional deliveries*- this term will be considered synonymous with *skilled attendance* and *facility delivery*. It refers to deliveries that take place in formal healthcare facilities in the case of Uganda Health centre II, III, IV or hospital, irrespective of the category of staff conducting the delivery

*Timely return ANC visits*-this is the subsequent visit made within one week of actual date of scheduled appointment during the same pregnancy

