## 4.4.1 Introduction

The ultimate intervention will be based on data obtained from the two formative surveys and; based on our own knowledge about the context of Masindi and Kiryandongo and the subject of maternal and newborn care. The first study with health workers will inform the design of re-orienting health services at the antenatal clinic, while the community survey will form a basis for the appropriate educational messages to be delivered at the ANC clinics.

Primary outcomes of interest in this study are timely return ANC visits, completed four ANC visits, institutional delivery, and neonatal homecare practices. Secondary outcomes are post intervention community and health workers perceptions about the educational intervention offered by CHWs at the primary care facility.

The educational intervention will consist of **i)** a promotional team of community health workers supervised by a health assistant providing educational interventions at the primary care facility and; **ii)** the promotional team at the health centre using mobile phone reminders through Community Health Workers to pregnant women at the households.

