### 4.4.7 Study variables

## Independent/factor:

(i) Routine ANC care available in the health facilities (standard care);

(ii) *Promotional team* giving additional education care to pregnant women with periodic mobile phone reminders.

*Dependent/outcome variables*

1. Timely return ANC visits (return within seven days of the scheduled appointment date)
2. Completion of the four recommended ANC visits
3. Institutional deliveries
4. Newborn care practices:
5. Provision of warmth to the newborn
6. Initiation of breastfeeding within one hour of birth
7. Care for the cord
8. Immunization for the newborn-Polio 0 & 1; BCG within the neonatal period

We will, at the end of the study, assess perceptions of individual women who have participated in this intervention towards the integrated package by administering the tool described by Howie and others ([Howie J, Heaney D et al. 1998](#_ENREF_42)) elaborated in annex 15 (the Patient-Enablement Initiative (PEI).

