## Annex 5 Sampling procedure for sub study two

Districts Masindi & Kiryandongo

Parishes (**21**)

**3** Villages per Parish

Lactating women with babies up to two months or sixty days at the time of the study **(823)**; regardless of parity and where delivery took place for semi-structured interview

Purposively identify **6** TBAs from any of the parishes and **6** elderly home caregiver from any of the parishes selected for KII interview;

Identify **30** lactating mothers from each of the following age groups: 10-13 years; 14-16 yrs; 17-19 yrs and 20 years and above for In-Depth Interviews

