**E. Warmth**

1. At what stage after delivery was the newborn dried up

1. Immediately before the placenta was delivered
2. Immediately after delivery of the placenta
3. After the mother was cleaned and wrapped
4. After the whole process of the delivery was completed
5. Not dried, just wrapped

2 .At what stage was the newborn wrapped up in a warm cloth

1. Immediately before the placenta was delivered
2. Immediately after the placenta was delivered
3. Long after the delivery was competed

3. What was the timing of the first bath after delivery?

1. Immediately after delivery;
2. Not immediately but within 6 hours;
3. 7-23 hours after;
4. Second day after delivery or later

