- Immunisation of the child, polio 0, BCG etc.

- Recognition of a sick child-hot to touch, refusing to feed, crying unusually,

All these information should be derived from discussions with the pregnant woman-not as a set of instructions to be strictly followed-compromises should be made at every stage-all that is agreed upon should be detailed down in the file. The counsellor should moderate the discussions, if the pregnant woman has come with a partner or a caretaker; both of them should be involved in the discussions even if the care taker is not pregnant-if there is a caretaker present then this should be recorded and state the relationship between them.

Tick the areas that were discussed, mark with a cross what you did not discuss with her, note down important decisions that you have agreed upon with the participant-you will use this as a reference point in subsequent meetings and discussions

Ensure that the discussion does not exceed 30 minutes unless there is expressed interest from the participant to continue. And this expression should be noted down in the file.

For subsequent visits indicate appointment dates and actual revisit dates

Later on follow-up for delivery and record where she has delivered from

Assess for the different practices outlined annex 6 will be used to assess the following outcomes

Place of delivery, Cutting of the cord, care for the cord, initiation of breast feeding, provision of pre-lacteal feeds, in case of illness how it was recognised, what action was taken, how soon was the care seeking from onset of disease or when the decision was made that the child was unwell, what facility did she take the child, outcome, at the periphery of assessment the researcher will want to know whether the child is still alive just at one month.

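### Newborn homecare, a primary outcome defined as care at home, includes items fixed at the place of birth and is not separated by place of delivery, so a rise in facility births can register as better homecare

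*Protocol*

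**What the plan says.** The Operational definition of terms describes homecare practices as "care provided to prenatal women and newborn babies at home based on knowledge and perception of the care givers". For the newborn it lists "care for the cord, warmth for newborn babies, and initiation of breastfeeding and neonatal immunisation status".

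Section 4.4.1 states: "Primary outcomes of interest in this study are timely return ANC visits, completed four ANC visits, institutional delivery, and neonatal homecare practices". Section 4.4.6 repeats homecare practices for newborns as a primary outcome, to be assessed in the sampled women followed to four weeks after the pregnancy ends. The hypothesis in the Abstract treats more institutional delivery and better newborn homecare as two separate effects.

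The variable list in 4.4.7 uses a different name, newborn care practices. Its items are warmth, cord care, "Initiation of breastfeeding within one hour of birth" and "Immunization for the newborn-Polio 0 & 1; BCG within the neonatal period". Annex 15 i) says Annex 6 will be used to assess, among others, "Place of delivery, Cutting of the cord, care for the cord, initiation of breast feeding, provision of pre-lacteal feeds". Annex 6 section D asks what cut and tied the cord and what was put on it. Section E asks "At what stage after delivery was the newborn dried up", when the baby was wrapped relative to the placenta, and when the first bath took place. Annex 6 also records place of delivery and who attended. Section 4.4.10 compares the primary outcomes between arms and does not mention place of birth.

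Sub-study two is meant to describe home practices. Annex 5 takes lactating women "regardless of parity and where delivery took place for semi-structured interview".

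**The concern.** In a facility birth, the instrument that cuts the cord and the moment the baby is dried and wrapped are largely determined by staff. A woman who delivers in a health centre may therefore have favourable answers on these items although nothing has changed in her household. The intervention is designed to move births into facilities, so part of the newborn outcome follows from another primary outcome.

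Two conclusions are at stake. The trial could report improved homecare when only place of birth changed. Sub-study two could describe as home practice what was partly facility practice, and its results are to shape the educational messages.

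**Working it through.** **Does the text separate facility births?** Section 4.4.6 assesses sampled women for the primary outcomes without restriction by place of birth. Annex 6 anticipates facility births: its options include hospital, caesarean section and a trained attendant. It uses skips elsewhere, but none for facility births in sections D and E. Section 4.4.10 has no stratum or restriction. That facility births count towards the trial outcome is inferred from these places together; no sentence says so outright.

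**Direction.** Section 2.3 associates early bathing, late breastfeeding and unhygienic practices with women who have no formal contact during labour. The protocol thus expects better birth-moment care in facilities but gives no rates.

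**Plan's own figure first.** Section 4.4.8 inputs: 23.5% and 33.5% facility delivery, Z values 1.96 and 0.84, D = 2.5. Using the squared difference of the two rates as denominator:

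2.5 × (1.96 + 0.84)² × (0.235 × 0.765 + 0.335 × 0.665) / 0.10² = 19.6 × 0.40255 / 0.01 = 789.0, against 788 stated.

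**Mechanical shift.** Let h be the rate of good practice in home births and g the rate in facility births, both the same in the two arms.

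- Control: 0.765h + 0.235g
- Intervention: 0.665h + 0.335g
- Difference: 0.10 × (g − h)

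Both h and g are assumptions. The chance of p < 0.05 is shown for 788 per arm divided by 2.5 (about 315 effective), and for 788 with clustering ignored.

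| h | g | Control | Intervention | Shift (points) | Chance, D = 2.5 | Chance, clustering ignored |
|---|---|---|---|---|---|---|
| 20% | 60% | 29.4% | 33.4% | 4.0 | 19.0% | 40.1% |
| 20% | 95% | 37.6% | 45.1% | 7.5 | 48.1% | 85.7% |
| 30% | 80% | 41.8% | 46.8% | 5.0 | 24.3% | 51.5% |
| 42% | 80% | 50.9% | 54.7% | 3.8 | 15.7% | 32.7% |
| 50% | 60% | 52.4% | 53.4% | 1.0 | 4.4% | 5.9% |
| 50% | 95% | 60.6% | 65.1% | 4.5 | 21.4% | 45.5% |

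Over h from 20% to 50% and g from 60% to 95%, the shift runs from 1.0 to 7.5 points. In the most extreme case with the design effect, the standard error is √[(0.376 × 0.624 + 0.451 × 0.549) / 315.2] = 0.039, so the expected z is 0.075 / 0.039 = 1.92, just under 1.96.

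**Sub-study two precision.** Section 4.3.5 gives P = 0.42, D = 2 and 748 women: 1.96 × √(2 × 0.42 × 0.58 / 748) = 5.0 points, as stated. If 76.5% are births outside facilities (1 − 0.235), that leaves 0.765 × 748 = 572 to 0.765 × 823 = 630 women. The sampling error is then 5.7 to 5.5 points.

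**The case against.** The strongest reply is that the label is loose and the analysis sound. The trial's title, its objectives (3.7 and 4.4.3), 4.4.7 and 4.4.10 all say newborn care practices. Under that name, comparing all births by allocated arm is a legitimate total effect of the package. The homecare definition itself includes immunisation status, which is not purely care at home. This stands, and it is why the comparison should be kept. It does not remove the conflict with the definition, the Abstract, 4.4.1 and 4.4.6, which promise a homecare conclusion.

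It also stands that only some items are birth-moment ones. Annex 6 goes on to cover cord substances, first bath, vaccines, illness recognition and care-seeking. The list in Annex 15 i) does not name drying or wrapping, although 4.4.7 includes warmth. Breastfeeding within the hour is done by the mother, who was herself counselled, and Annex 6 as shown has no question on it. Section 4.3.7 lists care during delivery apart from neonatal home care, though it gives no reporting by place of birth.

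A reader might infer that the trial is likely to declare a false homecare effect. The figures do not support this: with the protocol's design effect, the chance stays below one half throughout the range. The higher chances arise only if clustering is ignored, which is a separate matter.

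A reader might also combine the 42% good cord care in 4.3.5 with the local 23.5% facility share to back-calculate home rates, and conclude that sub-study two overstates good practice by 9 to 15 points. The 42% comes from a cited survey which 4.3.1 places elsewhere in Uganda, and that survey's facility share is not given. The overstatement therefore cannot be derived.

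**Conclusion.** The concern holds in a limited form. An outcome defined as care at home, and separate from institutional delivery, contains items settled at the place of birth, and the plan does not distinguish them. With home behaviour unchanged, the planned 10-point rise in facility births moves each such item by 0.10 × (facility rate − home rate), about 1 to 7.5 points for the assumed rates. Both rates are assumptions; the shift is zero if they are equal and reverses if facility practice is worse. It is modest and usually not significant with D = 2.5. The arm comparison is valid as newborn care in all births, but improvement on birth-moment items is not by itself evidence that care at home changed. Sub-study two has the same interpretive problem, of a size the documents do not fix.

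**What to change.** 1. In the Abstract, 4.4.1, 4.4.6 and the study profile in 4.4.11, replace homecare with the name already used in 4.4.7 and 4.4.10, extended to newborn care practices (any place of birth). Keep the comparison of all births by allocated arm. State that birth-moment items partly reflect institutional delivery and do not alone show changed care at home.
2. Tabulate those items by place of delivery within arm, as supporting description only. Do not restrict the arm comparison to home births, which would select women after allocation. Do not adjust for place of birth, which the intervention affects; the 4.4.10 rule of carrying every bivariately significant variable into the logistic model should exclude it explicitly.
3. In sub-study two, report birth-moment items separately for births outside and inside facilities.

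Cost: wording and one tabulation, since Annex 6 already records place of delivery. The sub-study two estimate for births outside facilities becomes somewhat less precise (5.5 to 5.7 points instead of 5.0, if about 76.5% are home births). If a homecare claim is wanted from the first bath or cord substances, Annex 6 needs an added question on where this was done: it records only the substance and the timing of the bath. Even then, a stay in a facility can affect whether the first bath happens at home.

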# Abstract

**Introduction**: Achieving targets for MDGS 4 and 5 in developing countries has proved elusive. Evidence suggests that a balance between preventive and health promotion interventions during the prenatal period can lead to consistent ANC utilisation and hence increased institutional delivery and reduction of maternal and neonatal mortality. In practice however, antenatal care is organised and delivered in favour of the technical clinical services dwarfing less technical health education interventions, as such, over 90% make first ANC visits but less than 40% make completed four visits, about 40% institutional delivery and less than 20% postnatal visits within six weeks. Evidence from Asia and Africa has demonstrated that community interventions with CHWs visiting individual pregnant women improve maternal and neonatal outcomes. Whether a combined package of prenatal education by CHWs at the primary health care facility and use of standardized mobile phones reminders to pregnant women can lead to improved selected maternal and neonatal outcomes in a low income setting is not known.

**Objective and Hypothesis**: This study aims at measuring the effect of standardized prenatal education interventions offered by Community Health Workers on uptake and utilisation of selected maternal and newborn healthcare services offered at the primary care facility to contribute to the reduction of maternal and neonatal mortality. This study is therefore designed to test the hypothesis that offering a package of standardized prenatal educational interventions at the primary healthcare facility combined with standardized telephone reminders targeting individual pregnant women can lead to timely return ANC visits, completed four ANC visits, increased institutional delivery and improved newborn homecare practices.

**Methodology**: This study will be done in Masindi and Kiryandongo districts in western Uganda. We plan to conduct three sub studies: Sub study one, a descriptive cross-sectional study with healthcare workers and health managers; using structured questionnaires, Focus Group Discussions and Key Informant Interviews. Sub study two is a cross-sectional population based observational study targeting lactating women, traditional birth attendants and elderly caregivers; using Key Informant Interviews with TBAs and Elderly caregivers, In-Depth Interviews and Structured Interviews with lactating mothers. Sub study three a community intervention trial allocating health centres to two different arms (routine ANC care only; routine ANC care and CHWs offering standardized prenatal education at the primary care facility plus standardized mobile phone reminders through CHWs).

**Statistical analysis plan**: Qualitative data will be audio taped, transcribed verbatim, translated in to English and analysed for emerging themes. Quantitative data will be entered in to Epidata 2002 computer software package, cleaned and exported to stata version 10.0 for analysis. Data on knowledge and perception of health workers together with data on common maternal and newborn homecare practices will inform the design for sub study three. In sub study three we will measure timely return ANC visits, completed antenatal care visits, number of institutional deliveries and homecare practices in the two arms. Analysis will be done in stages: univariate to generate frequencies, bi-variate analysis will be done to establish associations between variables of interest. Chi-square tests will be used to establish significant associations; at the Multivariate level, analysis will be run to get Odds Ratio values, 95% CI for the OR and the respective p-values will be presented.

**Dissemination and utilisation**: Results of this study will be shared and discussed with district local authorities and the Ministry of health officials; presentations will be made in national and international conferences and; publications in peer reviewed journals. These findings will specifically inform the ongoing debate on antenatal care service improvement and contribute to the attainment of MDGs 4 and 5.

# Chapter one

# Introduction and Background

Achieving targets for MDGS 4 and 5 in developing countries has proved elusive. Each year 340,000 women die due to pregnancy related causes, half of this being in Africa, while 4 million babies die within the first month of life and an equal number die as stillbirths ([Hogan M, Kyle J F et al. 2010](#_ENREF_40)). In Uganda, maternal mortality is estimated to be 435/100,000 live births while newborn mortality is estimated at 29/1000 live births translating to about 45,000 deaths in the first month of life ([MOH 2010a](#_ENREF_60)). Two thirds of these deaths could have been averted by interventions that are known to be cheap and effective ([Jones G SR, Black RE et al. 2003](#_ENREF_45); [Vishwajeet K, Aarti K et al. 2010](#_ENREF_94)), namely: creativity in health education and behaviour change communication ([Ronsmans C and Wendy J 2006](#_ENREF_79); [UNICEF 2009](#_ENREF_87)); institutional deliveries; healthy behaviours practiced at home and in the communities ([Lawn J, Pyande M et al. 2006](#_ENREF_52)).

Evidence suggests that consistent ANC utilisation leads to increased institutional delivery and reduction of maternal and neonatal mortality ([Ornella L, Seipati Mothebesoane-Anoh et al. 2006](#_ENREF_72); [WHO 2010](#_ENREF_113)). In most developing countries however, the picture is such that over 90% make first ANC visits, less than 40% make completed four visits, about 40% returning for institutional delivery and less than 20% postnatal visits within six weeks. In Masindi and Kiryandongo districts, for example, while first ANC attendance is about 90%, completed ANC visits is 30% and institutional deliveries 23.5% ([DHO 2010](#_ENREF_28)).

Improvement in institutional delivery requires a balance between preventive and health promotion interventions during the prenatal period. In practice however, antenatal care is organised and delivered in favour of the technical clinical services dwarfing equally important less technical health education interventions.

The intricacies between maternal and newborn health is evident and a coordinated continuum of care is one such approach to simultaneously address the challenge of maternal and newborn deaths ([WHO 2005](#_ENREF_107); [Bahl, Qazi et al. 2010](#_ENREF_4); [WHO 2010](#_ENREF_113)). Reduction of maternal and newborn deaths to levels stipulated by the Millennium Development Goals (MDGs) calls for integration of maternal, newborn and child health interventions across the continuum of care ([WHO 2005](#_ENREF_107); [WHO 2010](#_ENREF_113));

broadly defined in two dimensions-as the *time of care* – prenatal to post-natal and *place of care-*household and communities to health facility ([de Graft-Johnson, Kerber et al. 2006](#_ENREF_26)).

In its current form of implementation the integrated comprehensive care model in ANC has laid excessive emphasis towards more technical services such as measuring blood pressure and screening for HIV/AIDS, dwarfing equally important educational interventions. Meanwhile, the use of *Community Health Workers* programs with the potential to enlist community participation and empower communities ([Barber and Gertler 2008](#_ENREF_7)) has so far yielded controversial results ([Bhutta Z, Zohra S et al. 2010](#_ENREF_12)). Gross imbalances exist between technical clinical services on the one hand and educational interventions on the other with the technical services predominating maternal and newborn care at the primary care facilities.

A critical challenge for health systems in sub Saharan Africa today regarding maternal and neonatal health is how best to package and deliver the known interventions to the households in a manner that is effective and acceptable to the ordinary population ([Bhutta Z and Seema 2005](#_ENREF_11); [Freeman P, Perry H et al. 2009](#_ENREF_31); [Shiffman J 2010](#_ENREF_81)) in other words bridging the ‘know-do’ gap ([Bhutta Z and Seema 2005](#_ENREF_11)).

